**[name] (Noarlunga GP Plus)**

**[name] (ICCNet)**

**Associate Investigators: [name]**

**[name]**

**[name]**

**[name]**

**[name] (Study RA; Masters student)**

**Introduction**:

Heart failure (HF) is a complex clinical syndrome characterized by the reduced ability of the heart to pump and/or fill with blood, causing a significant burden for patients and healthcare systems in developed countries. HF is increasing in prevalence affecting at least 26 million people worldwide (Savarese & Lund, 2017). HF accounts for approximately 1-3% of overall healthcare spending, mainly due to repeated hospital admissions and prolonged inpatient length of stay (Sahle et al., 2016). However, the return of investment in healthcare spending in HF is very poor as studies suggest that approximately 50–75 % of patients with HF die within five years of diagnosis and this expenditure has been estimated to increase dramatically with an ageing population (Sahle et al., 2016).

Despite the significant advances in therapies and prevention, non-adherence with medication in HF patients is associated with excess mortality and morbidity. Medication adherence is defined as the extent to which a patient takes medications as prescribed by their healthcare providers (Chowdhury et al., 2013). While the World Health Organization describes poor adherence as ‘a worldwide problem of striking magnitude,’ it is a problem that should be viewed as ‘diagnosable and treatable’ (Marcum et al., 2013; WHO, 2003).

A systematic review estimated adherence to medications for HF to be 48.4% (95% CI 9.0% to 89.2%) (Bowry et al., 2011). Suboptimal adherence is recognized as a global challenge to health systems, due to its strong association with an increased risk for poor health, adverse outcomes and mortality (Forsytha et al., 2019; Hines et al., 2018). For example, Chowdhury et al. estimate that of all adverse medication reaction-related hospital admissions in the USA, 33–69% are due to poor medication adherence with an estimated cost of $100 billion (Chowdhury et al., 2013).

While Bowry et al. (2011) report that adherence does not significantly change according to gender, age or the complexity of medication regimens, factors which significantly influence adherence levels are low social status, low health literacy, existence of co-morbid conditions, and polypharmacy (Bowry et al., 2011). Other common predictors of poor adherence include negative perceptions about medication, side effects and high medication costs (Bowry et al., 2011). Furthermore, self-efficacy for appropriately taking HF medications may be predictive for physical health status where individuals with higher self-efficacy report better physical health status, including symptom control, and quality of life. Clinically, higher self-efficacy has been found to improve cardiac function, which may explain improvements in physical health status as symptom burden is less. Consequently, supporting people’s self-efficacy and confidence in their selfcare activities will impact their medication adherence, condition control and health status (Como 2018).

The use of the internet and smartphones to deliver health care is growing rapidly (Becker et al., 2013). Mobile health (mHealth) interventions, such as smartphone applications (apps), have been advocated as promising strategies to assist in the self-management of hypertension and other chronic conditions. The number of smartphones worldwide is predicted to reach 5.8 billion by 2020 and there are 6 million multimedia applications (apps), of which 318,000 are mHealth apps, available for download in the app stores (Byambarsuren et al., 2018). With the global prevalence of mobile technology, accessing health-related applications via mobile phone seems a logical step in the patients’ management of their own medical conditions. While there is still a threefold ‘‘digital divide’’ between age groups, sexes and according to education levels, it seems likely that mHealth apps will increasingly play a role for elderly and chronically ill users (Becker et al., 2013). However, guidance and coaching by the healthcare provider will be necessary and not overloading an application with functionality is essential when developing for elderly users with chronic conditions (Becker et al., 2013).

Electronic devices are increasingly used by both health care providers and patients as communication tools. Providers using mobile communication technology to connect with their patients achieve an improved overall patient-provider communication, strengthened patient autonomy, and empowered patients to tackle daily health issues (Becker et al., 2013). Studies from various clinical contexts, in which text-messaging services were introduced, reported improved medication adherence (Morawski et al., 2018; Becker et al., 2013). mHealth tools have the potential to address nonadherence by providing reminders for medication taking and refilling, tracking biometric results, offering education and facilitating social interactions that provide support and motivation. By assisting the patient to actively measure, monitor and manage their health condition, mHealth apps promise to improve health outcomes.

While technologies, such as smartphone apps, are promising tools to help reduce the global problem of non-adherence to long-term medications further evidence is needed to help guide health professionals and health services. The present study aimed to determine whether a personalized progressive reminder system using the NPS MedicineWise app will improve medication adherence in HF.

**Hypothesis**:

The primary hypothesis is that reminders via a smartphone application with a personalized and progressive monitoring system plus usual care (as received by participants in the intervention arm) compared with usual care alone (as received by participants in the control arm) will be associated with higher medication adherence, at 9 months’ follow up.

The secondary aims of this trial includes:

1. to determine whether a smartphone application reminder with interactive and personalised monitoring is cost effective, as determined by lower health services utilization, at 9 months’ follow up;

2. to determine the impact of the smartphone application on signs and symptoms of heart failure and quality of life at 6 and 9 months;

3. to determine whether the intervention is associated with higher medication and heart failure knowledge;

4. to determine the feasibility, acceptability and engagement with the application as determined by the

**Methods and Analysis**

This protocol is reported in accord with the Standard Protocol Items: Recommendations for Interventional Trials (SPIRIT) 2013 guidelines for protocols of clinical trials (Chan et al., 2013).

**Design**

The study is a prospective, single-blind observational RCT with individual participant allocated to the intervention or control group (Figure 1). Participants randomized in the control arm will be blinded to the intervention. Researchers undertaking the data collection will not be blinded due to the personliased and progressive monitoring nature of the intervention arm.

**Setting**

The study will be conducted in six investigator centres in South Australia: five South Australian metropolitan hospitals (Royal Adelaide Hospital, Queen Elizabeth Hospital, Lyell McEwin Hospital, Flinders Medical Centre and Noarlunga Hospital) and rural patients will be recruited from integrated Cardiovascular Clinical Network (ICCNet). A total of 220 patients will be recruited and randomized to either the intervention arm or control arm of the study. Eligible participants will be briefed about the study by the treating physician or nurse and they would then be referred to a member of the research team either in person or by skype call when participants come into the hospital for their regular outpatient clinic visits, when the community cardiac nursing team visit patients at home or, in the case of rural patients, during their scheduled skype ‘visit’ with cardiac nurses. Potential participants will be provided with a summary study information and will be contacted by the research team for an initial face-to-face interview either at any of the participating hospitals or via skype for rural patients. At this initial visit, after screening for eligibility, written informed consent will be obtained from those who agree to participate in the study and a baseline assessment will be completed by a member of the research team. A record of non-participation will be kept for those who are ineligible or those who decline to participate in the study. Follow ups at months 3, 6 and 9 will be conducted over phone or skype by a member of the research team.

**Study population**

Entry criteria are as follows: (i) age 18 years or older and able to give written informed consent; (ii) confirmed diagnosis of systolic heart failure on echocardiography (iii) NYHA functional class I-III for at least 3 months; (iv) Left ventricular ejection fraction (LVEF) < 50 % at or around the time of diagnosis of heart failure in keeping with the 2018 Australian Heart Failure guidelines (which will also include patients with an improved, or recovered ejection fraction of >50% following treatment)(Atherton et al. 2018) (v) stable or stabilized condition (vi) Participant or carer with access to a smartphone or similar smart device and have adequate access for receiving and responding to emails and skype calls.

Exclusion criteria includes: (i) palliative heart failure (ii) NYHA functional class IV (iii) malignancy or diastolic heart failure (iv) unable to understand the study information or unable to complete outcome questionnaires (ie. if an interpreter is required) (v) life expectancy less than 6 months or patients engaged with the palliative care network (vi) use of other medication reminder app or other electronic reminder systems for daily administration of medications; (vii) participant or carer who do not have access to a smartphone or similar device or do not have adequate access for receiving and responding to emails and skype calls.

Participants are free to withdraw from the study at any point in time and this will not impact their on-going care. This will be emphasized during the consent process. If a participant chooses to withdraw, the reason for withdrawal will be requested and recorded. All data collected to the point of withdrawal will not be included in the final analysis.

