**Randomisation and blinding**

Participants will be randomly allocated in a 1:1 ratio to either intervention or control group arms. Randomising of study participants will be done according to the random number generator from <https://www.random.org/integers/?num=220&min=1&max=220&col=5&base=10&format=html&rnd=new>. Participants allocated even numbers will be cases and participants allocated odd numbers will be controls. Participants randomized in the control arm will be blinded to the intervention. Due to the nature of the intervention, it will not be possible to blind the investigators. However, to minimize bias, all participants will be allocated a study ID and all data will be collated using the study ID. Analysis of the data will be conducted by blinded investigators.

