**Intervention**

The intervention was developed based on the principle of cued actions of the Health Belief Model (Strecher and Rosenstock. 1997). This model states that external cues, such as reminders and prompts, may increase adherence behaviours.

Usual care arm

Participants randomised to the usual care arm will receive standard care for their HF as determined by their treating physicians, including prescriptions to treat CHF and advice, as well as lifestyle advice. The participants in this group will have no access to a smartphone medication reminder application.

Intervention arm

Participants allocated to the intervention arm will have access to the NPS MedicineWise application (MedicineWise app) in addition to standard care (as described above). Once consented, each participant in the intervention arm will be given training by a member of the research team. This training will include how to download the MedicineWise app from the participant’s smartphone application store, navigate the features within the MedicineWise app, how to enter all of their current medications (both CHF related and non-related) into the app (including medication name, strength, dosage form, dose and frequency of administration), how to edit or delete a medication if there are instructed changes from their treating physician, how to set up in-app reminders, how to acknowledge and register a taken dose and troubleshooting and technical support information. The researcher will also provide practical tips to ensure participants can get the best experience from their interactions with the app. instruct participants in the intervention arm how to edit or delete a medication if the medication, dose or timing is either changed or suspended by their treating physician. At the end of the training, participants will be asked to demonstrate to the researcher team member that they can perform these functions on the app comfortably and that they know where and how to seek help should any problems occur.

Tier 1 intervention: in-app medicine dose reminders from the MedicineWise app

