**Trial data collection**

Trial data will be collected at 4 time points (at baseline, 3, 6 and 9 months). Data will be collected at face-to-face during home visits, phone calls or via skype interviews (mainly for rural participants). To encourage participant retention and completeness of data, participants will receive a honourarium of AUD$30 in total at completion of the study.

At the point of recruitment into the trial, baseline data will be collected after written informed has been obtained by a member of the research team. The following information will be collected:

Sociodemographic information: Date of birth, gender, ethnicity, height, weight, education status, marital status, employment status, smoking status and health literacy

Medical history: comorbidities, NYHA class, standardised mini-mental state exam score, depression score, all prescribed and non-prescribed medication history

Laboratory test results: full blood counts, full electrolytes (sodium, potassium, urea, creatinine +/- magnesium), Hb, iron studies, NT pro BNP, liver function tests.

Functional assessment: QoL questionnaire using the Short Form 36 Health Survey version 2 (SF-36v2) (Ware JE; RAND Corporation 2015), Depression Anxiety and Stress Scales (DASS), Self-Care of Heart Failure Index (SCHFI) (Riegel et al., 2009), EQ-5D-5L questionnaire (Herdman et al., 2011) and drug adherence questionnaire, healthcare utilization (linkage data from Australian Pharmaceutical benefits Scheme and Medicare Benefits Schedule).

At the 3, 6 and 9 month follow ups, a member of the research team will record details of any changes to the participants’ medication or implantable cardiac devices, details of any hospitalisations or healthcare resource utilization since the last follow up. At each follow up interview, participants in the control arm will be asked whether they have used any drug administration aids or medication reminder app or other forms of electronic reminder systems for daily administration of medications. At the end of the study, intervention arm participants will complete a satisfaction survey to assess the acceptability, utility and engagement with the NPS MedicineWise application. Also, data about prescription refill rates and healthcare utilization will be gathered for all participants through data linkage with the Australian Pharmaceutical benefits Scheme and Medicare Benefits Schedule.

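### Exclusion (vi) bars only *other* reminder apps, so read literally an existing NPS MedicineWise user is eligible and could be randomised to the no-app control arm

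*Protocol*

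**What the plan says.** Exclusion (vi) in Study population removes patients with "use of other medication reminder app or other electronic reminder systems for daily administration of medications". None of the other inclusion or exclusion criteria mentions current or past use of a reminder app.

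Under Intervention, the trial app defines the active arm: "Participants allocated to the intervention arm will have access to the NPS MedicineWise application (MedicineWise app) in addition to standard care". Training covers "how to download the MedicineWise app from the participant’s smartphone application store", so the app is a public product. The usual care arm is described without qualification: "The participants in this group will have no access to a smartphone medication reminder application".

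Randomisation and blinding sets the allocation ("Participants will be randomly allocated in a 1:1 ratio to either intervention or control group arms") and adds: "Participants randomized in the control arm will be blinded to the intervention".

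Trial data collection provides one check on app use. At each follow-up interview (3, 6 and 9 months), "participants in the control arm will be asked whether they have used any drug administration aids or medication reminder app", or other kinds of electronic reminder. The baseline data list in the same section has no item on app use.

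**The concern.** The entry rule and the description of the control arm do not match. The entry rule concerns apps *other* than an unnamed reference app; the control arm is to have no reminder app at all. A patient who already has MedicineWise with reminders set falls between the two: eligible under the first, and incompatible with the second once allocated to control.

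Such a control would already receive Tier 1, the in-app dose reminders. It would also be hard to call that person blinded to the intervention. Under the stated intention-to-treat approach the participant stays in the control group, and the 9-month difference is pulled toward zero. Because this is settled at entry, a question put to controls after randomisation can reveal it but cannot undo it.

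**Working it through.** **Step 1: does any other passage close the gap?**

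- *Inclusion criteria:* they require access to a smartphone or similar device and say nothing on app use.
- *Setting; Recruitment of participants:* screening is against the same written criteria, with no separate app question.
- *Baseline data:* no item on app use.
- *Usual care arm:* states what controls will have. It is not an eligibility rule, and no means is given of removing an app that a patient already has.
- *Follow-up question:* broad enough to catch MedicineWise, but asked only after randomisation.

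Nothing closes it.

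**Step 2: reproduce the plan's sample size.** Inputs from Sample size: 60% against 80% adherent, two-sided 0.05, power 80%.

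n = [1.96·√(2·0.70·0.30) + 0.8416·√(0.60·0.40 + 0.80·0.20)]² / 0.20² = (1.2702 + 0.5323)² / 0.04 = 81.2

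With continuity correction: (81.2/4)·[1 + √(1 + 4/(81.2·0.20))]² = 90.9, so 91 per arm and 182 in total. This matches the Protocol and shows that the correction was used.

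**Step 3: illustrate the dilution.** Let f be the share of controls already using the app. The Protocol gives no f, so all values are assumptions. Give these controls the full planned benefit and hold the intervention arm at 80%:

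control rate = 0.60 + 0.20·f; d = 0.80 − control rate = 0.20·(1 − f)

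power = Φ{[(d − 1/n)·√n − 1.96·√(2·p̄·(1 − p̄))] / √(p₁(1 − p₁) + p₂(1 − p₂))}, with n = 91 and p̄ the mean of the two rates

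- f = 0: [(0.20 − 0.0110)·9.539 − 1.2702] / 0.6325 = 0.843, power 80.0%
- f = 5%: [(0.19 − 0.0110)·9.539 − 1.2641] / 0.6308 = 0.703, power 75.9%

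The last column uses the plan's other calculation: difference 15·(1 − f), SD 35, 86 per arm.

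| f (assumed) | Control rate | Contrast (points) | Power, corrected | Power, uncorrected | Power, means |
|---|---|---|---|---|---|
| 0 | 60.0% | 20.0 | 80.0% | 84.3% | 80.2% |
| 2% | 60.4% | 19.6 | 78.4% | 83.0% | 78.6% |
| 5% | 61.0% | 19.0 | 75.9% | 80.8% | 76.1% |
| 10% | 62.0% | 18.0 | 71.4% | 76.7% | 71.5% |

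**Step 4: allow for Tier 1 only.** A control with the public app would have the in-app reminders, but not the trial's daily data review with personalised push messages (Tier 2) or pharmacist calls (Tier 3). If Tier 1 gave half the benefit (assumed), the control rate would be 0.60 + 0.10·f. At f = 10% that is 61%, the same as the 5% row: power 75.9% rather than 71.4%.

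**The case against.** The best defence is that the intent is plain. The usual care description excludes reminder apps without exception. The follow-up question to controls is equally broad, and there *other* clearly means electronic systems besides an app. The second *other* in exclusion (vi) can be read that way too. On this view the criterion is loosely drafted and any sensible recruiter would apply it as *any*. That stands as an account of intent, and a reader should not infer that the Protocol deliberately admits existing users. It does not remove the point: the first *other* qualifies the reminder app itself, and staff screen against what is written.

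A second defence is that the effect may be trivial. Nothing in the Protocol suggests that many of these patients already use this one app. At 2% the corrected power loss is under two points even with full benefit assumed, and without the continuity correction power is still 80.8% at 5%. This stands as well, and it limits the weight of the point.

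Third, the follow-up question gives partial handling: it measures contamination among controls and would support a sensitivity analysis. That is true, but it acts only after randomisation.

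A reader might also infer that a baseline SEAMS score measured under the app biases the primary analysis. The Protocol does not support this. Data analysis describes a comparison between arms at each time point, by t-test or chi-squared test, and not change from baseline.

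**Conclusion.** The point holds as a wording defect with an uncertain consequence. As written, exclusion (vi) leaves existing MedicineWise users eligible, and this conflicts with the description of the usual care arm. *Any* was probably intended.

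The direction is dilution toward no effect. Since randomisation spreads prior users over both arms, this mechanism would not manufacture an apparent benefit. The size cannot be fixed from the Protocol. On the plan's own 91 per arm with continuity correction, power falls from 80% to about 78%, 76% and 71% if 2%, 5% and 10% of controls are prior users. These are upper bounds on the loss at each prevalence, because they credit such controls with the full three-tier benefit when they would have Tier 1 only. It would be wrong to read them as an expected loss: the prevalences are assumed. The correction is worth making because it costs almost nothing, not because a large loss has been shown.

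**What to change.** Reword exclusion (vi) along these lines: *current use of any medication reminder app, including NPS MedicineWise, or of any electronic reminder system for daily medicines*. Put the question to every candidate at screening, before randomisation, so that it applies equally to both arms.

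The cost is one line in the criteria and one screening question. The downside is that a few current users become ineligible. The planned figures (86 and 91 per arm, 220 in total) do not change.

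The user-ID map described under the data captured by the app cannot take the place of this question. It is built once participants have downloaded the app and registered, and the dataset it serves covers the intervention arm only, so it would come too late and would miss controls.

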**Outcome measures**

Outcome measures will be collected at 3, 6 and 9 months following the baseline data collection at recruitment.

Primary outcome

The primary outcome is the comparison of medication adherence between the two arms. Medication adherence will be measured by self-reported medication adherence tool Self-Efficacy for Appropriate Medication Use Scale (SEAMS) (Risser et al., 2007). This has been validated previously in other cardiac conditions such as coronary heart disease (Risser et al., 2007). This self-reported data will also be verified by the data collected from the intervention arm participants whose adherence rate has been captured by the data collected by the NPS MedicineWise application.

Secondary outcomes

i. composite outcome of death or hospital admission related to HF or not related to HF. All instances of hospitalization and death will be recorded and classification as to whether it was HF related or not will be done by experienced cardiologists

ii. health resource utilization (ie. Primary and secondary care contacts, social care contacts and relevant medication use)

iii. health related quality of life, assessed by EQ-5D-5L

iv. self-reported medication adherence

v. assessment of exercise tolerance (6 min walk test)

vi. psychological wellbeing (Depression anxiety and stress scales)

vii. self-care of HF index questionnaire

viii. medication knowledge

ix. acceptability, utility and engagement with the NPS MedicineWise application (Satisfaction survey)

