**Data analysis**

The primary analyses will be based on a between-group (intervention arm vs control arm), intention-to-treat approach at the different time points. Continuous variables will be analysed using independent t-tests and discreet variables will be analyses using chi-squared tests. Where appropriate, other statistical tests will be employed depending on the nature of the data. Identification of any confounding baseline variables will be corrected by logistic regression analysis. All between group outcome results that are significant will be reported with odds ratios and 95 % confidence intervals. Statistical significance is set at α 0.05.

Qualitative outcomes

Thematic analysis will be carried out based on patient responses to open-ended questions in the functional assessments. This will enable to generate emerging and overarching themes. The analysis will characterise intervention arm participants’ observed and self-reported responses to the intervention and link these responses to the acceptability, utility and their engagement with the smartphone app. This thematic analysis will be based on the intervention arm participants’ responses collected at months 3 and 9, in addition to a satisfaction survey undertaken upon completion of the trial.

Economic outcomes

Data on the frequency and duration of hospital in-patient admissions will be obtained from medical records, and PBS and MBS utilisation data from Medicare following informed patient (or proxy in the case of moderate to severe cognitive impairment) consent. Unit costs will be derived from relevant hospital finance departments, published data sets including Pharmaceutical Benefits Scheme and Medicare Benefits Schedule and Australian Refined Diagnosis Related Groups (AR-DRG) cost weights.

A participant level analysis will be undertaken to determine the incremental costs and outcomes associated with the intervention relative to controls. Incremental cost effectiveness ratios and their associated confidence intervals will be estimated and cost effectiveness acceptability curves for varying threshold values of cost effectiveness will also be presented. An assessment of the sensitivity of the results obtained to variation in measured resource use, effectiveness and/or unit costs will be undertaken using appropriate one-way, multi-way and probabilistic sensitivity analysis.

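### The rule that drops all data from participants who withdraw contradicts the intention-to-treat primary analysis and should be replaced

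*Protocol*

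**What the plan says.** The last paragraph of the protocol's Study population section sets the rule for withdrawal. It is open as to time: "Participants are free to withdraw from the study at any point in time and this will not impact their on-going care". The reason is documented: "If a participant chooses to withdraw, the reason for withdrawal will be requested and recorded". The data are then removed whatever that reason is: "All data collected to the point of withdrawal will not be included in the final analysis".

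The Data analysis section states the analysis principle: "The primary analyses will be based on a between-group (intervention arm vs control arm), intention-to-treat approach at the different time points". It names t-tests for continuous and chi-squared tests for discrete variables.

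Under Outcome measures, "The primary outcome is the comparison of medication adherence between the two arms", measured with the SEAMS self-report scale, and "Outcome measures will be collected at 3, 6 and 9 months following the baseline data collection at recruitment". The Hypothesis section places the primary question at 9 months: the intervention "will be associated with higher medication adherence, at 9 months’ follow up". Secondary outcomes include a composite of death or hospital admission, and health resource utilisation.

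**The concern.** Intention-to-treat keeps randomised participants in the arm to which they were allocated and does not use later events to decide who counts. The withdrawal rule does the opposite: it removes a randomised person, with outcomes already observed, because of a later choice. It is not confined to people who ask for their data to be deleted, so it cannot be read as a consent safeguard only.

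Two things are at stake. The first is certain: valid data are lost. Someone who withdraws in month 8 loses completed 3- and 6-month assessments, and any earlier admissions and resource use that would have entered the composite outcome and the economic evaluation.

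The second is conditional. If withdrawal differs between arms and is related to adherence, the people left in each arm are no longer comparable. The design makes this plausible, because only the intervention arm receives alarms, push messages triggered by doses not marked as taken, and pharmacist calls. The protocol gives no withdrawal rate by arm and does not say that withdrawers are less adherent.

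**Working it through.** **1. The two rules side by side**

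| Question | Study population | Data analysis |
|---|---|---|
| Who is analysed? | Withdrawn participants are out | Intention-to-treat, no exception stated |
| Does the reason matter? | Recorded, but no effect on exclusion | Not mentioned |
| Observed 3- and 6-month data of a later withdrawer | Deleted | Belong in the analyses at those time points |

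Nothing else in the protocol reconciles the two columns.

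**2. What the sample size covers**

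The Sample size section reproduces. A 15-point difference with SD 35 needs 86 per arm. Proportions of 60% versus 80% need 91 per arm with a continuity correction. 91 × 1.2 = 109.2, rounded up to 110 per arm, or 220 in total. If 20% are lost from each arm, 110 × 0.8 = 88 remain, and power is about 81% for the means and about 83% for the proportions (normal approximation, no continuity correction). Numbers alone are therefore not the main worry. The allowance protects the count, not the comparability of the arms.

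**3. Illustration of selective loss**

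From the protocol: 110 per arm, 60% adherent, two-sided 5% level. Assumed: no true effect, the withdrawal fraction *w* in each arm, and the proportion *a* of withdrawers who are adherent.

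Analysed proportion: p = (0.60 − w·a)/(1 − w). Analysed number: 110(1 − w).

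The rejection probability is that of the pooled two-proportion z-test, Φ[(d − 1.96·SE₀)/SE₁] + Φ[(−d − 1.96·SE₀)/SE₁]. Here d is the difference in analysed proportions, and SE₀ and SE₁ are the pooled and unpooled standard errors.

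With 20% withdrawn from intervention (88 left) and 10% from control (99 left):

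- a = 0.60 (withdrawal unrelated to adherence): both arms stay at 60%, d = 0, type I error 5%.
- a = 0.30: intervention (0.60 − 0.06)/0.80 = 67.5%; control (0.60 − 0.03)/0.90 = 63.3%; d = 4.2 points. SE₀ = 0.0697, SE₁ = 0.0696. Type I error = 0.086 + 0.005, about 9%.
- a = 0: intervention 0.60/0.80 = 75.0%; control 0.60/0.90 = 66.7%; d = 8.3 points. SE₀ = 0.0668, SE₁ = 0.0661. Type I error = 0.236 + 0.001, about 24%.

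With 20% withdrawn from both arms and the same *a* in each, d = 0 and type I error is 5%. Both arms then look more adherent than they are: 67.5% for a = 0.30 and 75% for a = 0, instead of 60%.

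**4. What these figures measure**

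They describe selective loss of outcomes in general. They apply directly to the 3- and 6-month comparisons, where the rule deletes scores that exist. At 9 months, a participant who withdrew earlier has no score whether or not the earlier data are kept. A t-test or chi-squared test on 9-month scores would therefore show the same selective loss under either rule.

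**The case against.** The contradiction itself has no good answer. An unseen statistical analysis plan could only follow the rule or override it. The objections concern how far the consequences reach, and most of them stand.

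- **A reader might infer that the rule makes this a completers-only analysis.** It does not. It covers a participant who chooses to withdraw. It does not delete people who are lost to follow-up, miss a visit or die without withdrawing.
- **A reader might infer that the primary test certainly loses its 5% error rate in favour of the app.** The direction is an inference. A dose counts as missed when it is not marked as taken, so escalation also reaches people who take their medicine without tapping the app, and pharmacist contacts are capped at three. That every withdrawer is non-adherent is the extreme end of the range.
- **A reader might take the planned 20% loss, apply it to non-adherent intervention participants only, and report a false difference of 15 points with 61% type I error.** The arithmetic is right, but the Sample size section allows 20% in both arms, and for loss to follow-up rather than active withdrawal.
- **The primary scale is SEAMS, a score.** The proportions show the mechanism and do not predict a shift in SEAMS.
- **Keeping the data does not by itself repair the 9-month comparison**, as step 4 of the working shows.

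What remains is the direct conflict, the certain loss of observed data, and a possible bias that the rule does nothing to limit.

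**Conclusion.** The concern holds. The Study population and Data analysis sections conflict on who is in the primary analysis, and this rests on the text alone. The certain cost is the deletion of observed early outcomes, admissions and resource use of randomised participants.

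Bias is possible rather than established. Under the assumed 20% versus 10% withdrawal with no true effect, it ranges from none (withdrawal unrelated to adherence), through 4.2 points and about 9% type I error (30% of withdrawers adherent), to 8.3 points and about 24% (none adherent). Equal and equally selective withdrawal gives no false difference. These values rest on assumed withdrawal rates and a binary outcome. They bear on the deleted early visits, and should not be read as the error that the rule adds to the 9-month test.

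**What to change.** Replace the exclusion sentence in the Study population section with: *Data collected up to withdrawal will be retained and analysed in the randomised arm unless the participant explicitly asks for their removal.* Align the consent wording, and report withdrawals and their recorded reasons by arm.

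This needs one sentence in the protocol and no extra patients or visits. The consent pages were not available for this review, so what participants have already been promised, and how much work the alignment takes, could not be checked. The change is best made early, because people who consented under the deletion rule may limit what can be recovered later.

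If the retained visits are to inform the 9-month comparison, a likelihood-based repeated-measures model of the 3-, 6- and 9-month scores can be used, with the 9-month difference as the primary contrast. Its price is reliance on a missing-at-random assumption and a change from the stated t-test. It is a separate choice from the correction of the sentence.
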